## Methods

This study is a multicenter, prospective, non-blind, parallel-group, randomized controlled trial with the intervention group undergoing MuST procedure and a control group undergoing the RL technique. Patients will be randomized 1:1 to one of two CT, MUST or RL, and the follow-up period of this study will be 12 months. For each treatment group up to 100 patients are planned to be included.

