The key VA person and the nurse’s team will be carried out the following steps:Collect AVF photo, before the start of the study (baseline), at 6 months and at 1 year during the study;MuST cannulation technique – select and identify cannulation sites with a dermographic pen until their location is easily visible due to skin depigmentation; Two areas of arterial and venous cannulation will be created, with three cannulation points each at least 1 cm apart;Rope-ladder cannulation technique – create a diagram of the cannulation sites’ orientation. The diagram will be attached to each patient’s dialysis file for quick reference;AVF physical examination before each HD treatment with recording of the findings;The daily results of each patient’s assessment will be recorded using the computer tool VASACC (vascular access) and on an Excel spreadsheet;The nurse who performs the cannulation will assess the intensity of pain perceived by the patient;Pain will be assessed immediately after cannulation of the arterial and venous area according to the 10 cm long visual analog scale (VAS) which has the classification “No Pain” on the far left and “Extreme Pain” on the right [4, 17, 21];Whenever there is a referral to the Vascular Access Center (VAC) for angiography or vascular surgery, a record will be made in the patient’s clinical file in the EUCLID database;After the intervention in the VAC, a record of the intervention per patient will be made in the Vascular Access OnLine database (AV OnLine). This registration will be performed by the nephrologist or vascular surgeon, depending on which intervention is performed. This information will then be transcribed into the Excel data collection Spreadsheet;Patients will be followed until access thrombosis, abandonment due to AVF dysfunction or surgical intervention with anastomosis alteration, patient abandonment from the study, transfer to another clinic, hospitalization, death, change of treatment modality or study end;For the variable pain intensity, time to hemostasis, peri-needle bleeding, Qa, dialysis dose (*sp*kt/V) and substitution volume will be evaluated at 3 time periods only: before study start, at 6 months, and at 12 months;Presence of scab at the cannulation site and the ease of identifying the cannulation site will be evaluated at the same time periods, but only for CT MuST;Monthly meetings will be held with the head nurse and key VA person, and additional meetings whenever necessary. All situations deviating from normality there will be discussed. Verification and collection of data.

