### Study Outcomes

#### Primary outcome

As a primary indicator, we consider AVF survival rate at 12 months and determined by the percentage of fistulas in use from the time-zero of study enrollment to the date of the first clinical intervention by angioplasty or vascular surgery, to maintain or restore patency – "unassisted patency" [15, 16].

To assess the variable "AVF survival" we consider the following criteria:- Fistula that is successfully cannulated with two needles, arterial and venous, that allows a prescribed blood flow of at least 300 mL/min and that allows for an adequate treatment will be considered a functioning AVF [17];- Fistula used without success will be considered a dysfunctional AVF, whether it has patency or not [15];- It will be considered AVF abandonment on the day that access is considered permanently unusable or not suitable for cannulation [17];

Referral for endovascular intervention [15, 16] will be based on two of the following factors of AVF dysfunction:- Decreased AVF blood flow (Qa) (assessed by thermodilution and <400 mL/min);- Increased hemostasis time (>10 min);- Cannulation failure: failure or inability to insert dialysis needles [17];- Decreased dialysis efficacy: low HD dose, *sp*Kt/V <1.2 [17] or substitution volume <21L. A parameter to quantify the HD adequacy (*sp*Kt/V) will be calculated based on ionic dialysance obtained by the integrated module Online Clearance Monitor (OCM®) from the 5008 CorDiax machine, and “*V*” was derived from total body composition assessment with a bioimpedance device (Body Composition Monitor - FMC) [18];

Or changes in the physical examination (changes in thrill, abnormal development of aneurysm, or progressive increase in edema in the AV limb) and plus one of the factors described above.

Referral for surgical intervention [15] will be based on one or more indicators of AVF dysfunction:- Rupture of the AVF wall;- AVF thrombosis;- Progressive development of aneurysm;- Acute bleeding: AVF bleeding requiring surgical intervention;- Local infection of the AVF;- Deficient distal perfusion with signs of ischemia.

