### Statistical analysis

Data will be analyzed according to the “intention-to-treat” [15]. The continuous variables of the “baseline” will be expressed through measures of location, dispersion and the categorial variables will be summarized using absolute and relative frequencies. Descriptive comparisons and tests will be performed between groups at baseline, at 6 and 12 months. To compare two groups by continuous variables, parametric tests will be used, namely the t-test, or nonparametric tests if normality is not assumed.

To analyse relationship between categorical variables, the Chi-square test (χ^2^) will be conducted, or Fisher’s exact test when appropriate.

The primary factors to assess fistula survival will be calculated over time from baseline to time requiring intervention (no patency assistance) or withdrawal from the study. In this case we will use the Kaplan–Meier survival curves.

For secondary factors, such as the frequency of hematoma, signs of infection, local infection or bacteremia, and thrombosis, the number of events per 1000 days of AVF will be calculated [16].

Results will be considered significant when *p* < 0.05. All the statistical analysis will be performed using SPSS (version 23; IBM, Armonk, NY, USA).

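### Follow-up ends at any hospitalization or clinic transfer, which sits badly with a 12-month intention-to-treat endpoint, disagrees with the other end lists and may censor informatively

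*Protocol article*

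**What the plan says.** All places are in the protocol article.

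- **Intervention.** The rule begins "Patients will be followed until access thrombosis, abandonment due to AVF dysfunction or surgical intervention with anastomosis alteration" and continues "patient abandonment from the study, transfer to another clinic, hospitalization, death, change of treatment modality or study end". It sets no limit on the reason for admission or length of stay and does not provide for resuming observation afterwards.
- **Methods.** "the follow-up period of this study will be 12 months".
- **Primary outcome.** Fistula survival at 12 months, counted from enrolment "to the date of the first clinical intervention by angioplasty or vascular surgery, to maintain or restore patency".
- **Secondary outcome.** The second survival measure has its own end list: abandonment of the access or by the patient, death, change of modality, and study end. Hospitalization and transfer are absent.
- **Statistical analysis.** "Data will be analyzed according to the “intention-to-treat" is the stated principle. Primary survival time is "calculated over time from baseline to time requiring intervention (no patency assistance) or withdrawal from the study", and "In this case we will use the Kaplan–Meier survival curves".
- **Background.** Vascular access is described as a leading cause of hospital admission in hemodialysis patients.
- **Intervention, data sources.** Referrals to the Vascular Access Center are recorded in EuCliD, and interventions done there in AV OnLine.

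**The concern.** A hospital admission does not in itself end the life of a fistula. As written, a short admission for an unrelated illness would end observation of a fistula that is still in use, and any angioplasty or surgery later in the 12 months would fall outside follow-up.

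Two things are at stake. The first is information: primary events after the stop are not counted. The second is validity. Kaplan-Meier treats a censored patient as having the same later risk as those who remain under observation. The protocol's own Background makes that doubtful for access-related admissions, and several triggers for surgical referral under Primary outcome (wall rupture, acute bleeding, local infection, ischemia) could plausibly bring a patient into hospital before the procedure that counts as the event.

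This is a rule about what is observed. If data collection stops at admission, a later analysis plan cannot recover what was not collected.

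**Working it through.** **1. The end rules side by side**

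| Section | Hospitalization ends observation? | Transfer ends observation? |
|---|---|---|
| Intervention | yes | yes |
| Secondary outcome | not listed | not listed |
| Statistical analysis (primary) | not listed, unless withdrawal is meant to cover it | not listed, same proviso |

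No section says how a patient stopped for either reason enters the Kaplan-Meier analysis.

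**2. Events lost if these stops censor**

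The article gives no admission, transfer or event rate, so there is no figure to reproduce and every input here is an assumption. Let *s* be true 12-month unassisted patency and *h* the share of patients who would be stopped within 12 months. With independent exponential times, λe = −ln(s), λh = −ln(1−h), and

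observed event share = λe/(λe+λh) × [1 − s(1−h)], against 1 − s with full follow-up.

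Example, s = 0.70 and h = 0.20: λe = 0.357, λh = 0.223. Observed share = 0.357/0.580 × (1 − 0.56) = 0.271, against 0.300. Loss = 1 − 0.271/0.300 = 9.8%.

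| Stopped early (h) | Loss, s = 0.60 | Loss, s = 0.70 | Loss, s = 0.80 |
|---|---|---|---|
| 5% | 2.3% | 2.4% | 2.4% |
| 10% | 4.7% | 4.8% | 4.9% |
| 20% | 9.5% | 9.8% | 10.0% |
| 30% | 14.6% | 15.0% | 15.3% |
| 40% | 20.0% | 20.5% | 21.0% |
| 50% | 25.8% | 26.4% | 26.9% |

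A heavier assumption is a first-admission rate of 0.5 to 1.0 per patient-year, so that 1 − exp(−0.5) = 39% to 1 − exp(−1.0) = 63% are admitted. With 25% events (λe = 0.288), observed events are 19.9 to 16.2 per 100 instead of 25, a loss of 20-35%.

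**3. Effect on power**

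Take 70% against 80% patency, 100 per arm, two-sided 0.05. The hazard ratio is ln(0.80)/ln(0.70) = 0.626. Power ≈ Φ(√D/2 × |ln 0.626| − 1.96), where D is the number of events.

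- Full follow-up: D = 50, power 38%.
- 20% stopped early: D = 45, power 35%.
- 40% stopped early: D = 40, power 31%.

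**4. Bias if admission changes the risk**

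Let the event hazard be multiplied by *k* after admission. Kaplan-Meier with censoring at admission estimates *s*, the survival under the pre-admission hazard. True 12-month patency is

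s(1−h) + λh·s^k × [1 − exp(−c)]/c, with c = λh + λe − kλe.

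Example, s = 0.70, h = 0.20, k = 2: c = −0.134, so 0.56 + 0.223 × 0.49 × 1.070 = 0.677. Simulation with 400,000 patients per scenario gave the same value.

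| k | Kaplan-Meier estimate | True, 20% admitted | True, 40% admitted |
|---|---|---|---|
| 1 | 0.70 | 0.70 | 0.70 |
| 1.5 | 0.70 | 0.69 | 0.675 |
| 2 | 0.70 | 0.68 | 0.65 |
| 3 | 0.70 | 0.66 | 0.61 |

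For an estimate of 0.80 and k = 2, the true values are 0.783 (20% admitted) and 0.764 (40%).

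**5. What this does to the comparison**

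Suppose Kaplan-Meier shows 0.70 against 0.80, a difference of 10 points, and k = 2. With the same admission share in both arms the true difference is 0.783 − 0.677 = 10.6 points (20%) or 0.764 − 0.652 = 11.2 points (40%), so the contrast moves little. With unequal shares it moves more: 0.764 − 0.677 = 8.7 points if 20% are admitted in the lower arm and 40% in the upper, and 0.783 − 0.652 = 13.1 points the other way round.

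**The case against.** The strongest reply is that the Intervention text says how long patients are followed, not how they are analysed. The Statistical analysis section runs primary time to intervention or withdrawal and names neither hospitalization nor transfer, and registered interventions could still be counted after a stop. That stands as far as it goes: censoring at admission is the natural reading, not stated text. But it leaves the lists in disagreement, and the word withdrawal may or may not cover these stops.

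Four stronger readings are tempting, and the article does not support them.

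- *The rule contradicts intention-to-treat and the 12-month follow-up.* Intention-to-treat strictly means analysis by assigned group, and 12 months can be read as a maximum, since study end is one item in the same list. The rule undermines the aim of both without contradicting either literally.
- *Many primary events are discarded.* No rate is given. The loss could be near 2%, and it reaches 20% only when about 40% of patients stop early.
- *The worst complications drop out of the count.* Thrombosis is a separate stop in the same sentence, and Vascular Access Center referrals and interventions are recorded in databases. Infections are defined by positive cultures, and nothing says that the event behind an admission goes uncounted.
- *The censoring is informative.* The Background supports this for access-related admissions. It does not for unrelated admissions or for transfers, and with an unchanged hazard Kaplan-Meier is unbiased. A log-rank test is not named in the article, so nothing here rests on one.

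**Conclusion.** The point holds in a limited form. The follow-up rule ends observation for two reasons that are not the primary event, and it disagrees with the end points given under Secondary outcome and Statistical analysis. If it is applied as censoring, it weakens a 12-month intention-to-treat comparison.

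The share of primary events lost is unknown: about 2-27% if 5-50% of patients stop early, and 20-35% at an assumed 0.5-1.0 first admissions per patient-year. The effect on power is modest, from 38% to 35% or 31% in the example.

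Bias is the more serious possibility. If the hazard doubles or triples after admission and 20-40% are admitted, 12-month patency in an arm is overstated by about 2 to 9 points, against a sought improvement of 10% (Study hypotheses). Material distortion of the comparison would need admission patterns or post-admission risk to differ between arms, which the article neither shows nor excludes. All of these sizes rest on exponential times and assumed rates.

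**What to change.** - In the Intervention section, remove hospitalization as an end of observation for the primary outcome, and remove transfer wherever status can be obtained.
- State that every randomised patient is observed to 12 months for first angioplasty or vascular surgery, using the EuCliD and AV OnLine records.
- Censor a transferred patient only when status truly cannot be obtained, at the last date on which it was known.
- Give one end-of-observation list per outcome and use it consistently under Intervention, Secondary outcome and Statistical analysis, saying what withdrawal covers.
- Keep censoring at hospitalization and transfer, as now written, as a sensitivity analysis.

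This changes what is observed, not how patients are treated. For hospitalization the cost is small, because referrals and Vascular Access Center interventions are already recorded. For transfers, extra record checks are needed; neither their number nor whether receiving clinics report to the same databases is stated, so that effort cannot be sized from the article.

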### Study hypotheses

This study examines the following hypotheses:- Does MuST allow 10% rate of greater AVF survival in patients on a regular HD program in private HD clinics than RL?- Does MuST have a lower AVF complication rate in patients on a regular HD program in private HD clinics than RL?- Do patients submitted to MuST perceive less pain than patients submitted to RL?

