#### Inclusion criteria

Patients with AVF will be selected when:Are on a regular HD program with three weekly sessions;AVF has been in use for at least 8 weeks without incident;AVF with blood flow (Qa) ≥ 500 mL/min evaluated by thermodilution;AVF paths allow cannulations along the entire length of the vein with at least 6 cm of distance between bevels, or two distinct areas of 3 cm in length;Adult patients

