### Secondary outcome

We will evaluate the assisted primary patency. As an outcome, we considered AVF survival rate at 12 month and determined by the percentage of fistulas in use from the time-zero the study enrolment, to the date of access abandonment due to dysfunction, patient abandonment, or death, treatment change modality or study end [15, 17, 19]. For the study, we will consider the frequency of interventions, both endovascular and surgical, to maintain functioning access [17].

We will also include the following secondary outcomes associated with cannulation:- Inflammation signs at the AVF cannulation site, defined by the presence of one or more signs: redness, edema or local exudate [4];- AVF local infection, defined by the presence of exudate at the cannulation site with a positive bacteriological culture;- Bacteremia related with AVF and confirmed with a positive blood culture (describe if swab was performed and/or infection treated with antibiotics);- Hematoma or infiltration: an incident that occurs during cannulation that can result in local infiltration, edema, or pain, which can be treated with local ice, but re-cannulation is possible [16];- Time to hemostasis: time to stop bleeding after needle removal, with up to 10 min considered normal [4];- Peri-needle bleeding: bleeding from the puncture site during treatment and requiring nursing intervention;- Aneurysm development: segment dilatation of the arterialized vein at three times the diameter of the segment considered normal, which means a segment with a width of ≥ 18 mm [20]. An increase in the existing aneurysm will be considered when the vein presents an increase in its diameter of ≥ 5 mm.- Local pain related to CT;- Presence of scab at the cannulation site;- Easy to identify cannulation site.

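### Peri-needle bleeding is an in-session incident, yet it is evaluated at only three time periods, so 83% to 99% of follow-up sessions, including the change-over to the new MuST sites, go uncounted

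*Protocol article*

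**What the plan says.** All references are to the protocol article.

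- **Schedule (Intervention).** The list of restricted variables begins "For the variable pain intensity, time to hemostasis, peri-needle bleeding, Qa, dialysis dose", and these variables "will be evaluated at 3 time periods only: before study start, at 6 months, and at 12 months". The word *only* makes this a fixed rule, not detail left to another document.
- **Definition (Secondary outcome).** "Peri-needle bleeding: bleeding from the puncture site during treatment and requiring nursing intervention". It appears under the sentence "We will also include the following secondary outcomes associated with cannulation".
- **Hypothesis (Study hypotheses).** The second hypothesis asks: "Does MuST have a lower AVF complication rate in patients on a regular HD program in private HD clinics than RL"? The outcomes that make up this complication rate are not listed.
- **Recording at each session (Intervention).** The fistula is examined physically before every treatment, and "The daily results of each patient’s assessment will be recorded using the computer tool VASACC (vascular access) and on an Excel spreadsheet".
- **Analysis (Statistical analysis).** Hematoma, signs of infection, local infection or bacteremia, and thrombosis are to be expressed as events per 1000 days of AVF. They are given as examples, and peri-needle bleeding is not among them.

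**The concern.** Flow, dialysis dose, substitution volume, pain score and hemostasis time can each be measured at a chosen session, and a value at 6 and 12 months means something. Peri-needle bleeding is different: it either happens in a session or it does not, and a session that is not observed leaves no trace of it. Evaluating it at two points after the start samples a small part of the follow-up and says nothing about the rest.

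The gap falls where this trial has most reason to look. It deliberately enrolls fistulas already cannulated by other techniques, so each MuST patient has to establish new fixed sites, marked by pen until they are visible. A temporary excess of bleeding in that phase, or an early benefit, would not be counted. Follow-up also ends at thrombosis, abandonment, transfer, hospitalization or death. A patient who leaves before the 6-month evaluation contributes no post-baseline observation of this outcome, and such early exits may be informative.

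**Working it through.** The document gives no power, event rate or share of sessions observed for this outcome, so there is no stated figure to reproduce.

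**Inputs from the document**
- Session frequency (Inclusion criteria): "Are on a regular HD program with three weekly sessions".
- Duration (Methods): "the follow-up period of this study will be 12 months".
- Evaluations after the start (Intervention): two, at 6 and 12 months.
- Group size (Methods): up to 100 per arm.

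**Assumed, because the document does not say:** the length of a time period, taken as one session, one week (3 sessions) or one month (13 sessions).

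**Step 1: share of sessions observed.** Follow-up sessions per patient = 3 × 52 = 156. Observed sessions = 2 × sessions per period.

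| Length of a period | Observed | Share observed | Share unobserved |
|---|---|---|---|
| One session | 2 | 2/156 = 1.3% | 98.7% |
| One week | 6 | 6/156 = 3.8% | 96.2% |
| One month | 26 | 26/156 = 16.7% | 83.3% |

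In every row the first observed session after the start falls at about month 6.

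**Step 2: does other recording fill the gap?** The examination at each session takes place before treatment, whereas the outcome is bleeding during treatment. If the daily VASACC entry did capture bleeding, the restriction to three periods would still keep it out of the evaluation. The monthly meetings discuss deviations from normality, but that is not systematic counting of an outcome.

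**Step 3: illustration of the effect on power.** One model and one test are used for every schedule. Each patient has a gamma-distributed multiplier on the bleeding risk (mean 1, variance 2), the count is binomial over the observed sessions, and the arms are compared by a two-sided 5% t-test on square-root counts, with 100 patients per arm. The assumed risks are 2% versus 4% of sessions. Expected events per arm = 100 × observed sessions × risk.

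| Schedule | Expected events | Power |
|---|---|---|
| One session per period | 4 v 8 | about 20% |
| One week per period | 12 v 24 | about 41% |
| One month per period | 52 v 104 | about 70% |
| All 156 sessions | 312 v 624 | about 84% |

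With patient-effect variance 4, power for all sessions falls to about 56%. The model holds each patient's risk constant over the year, so it does not represent an early excess. It therefore shows only the loss on the average rate, not the loss from missing the change-over.

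**The case against.** **Period length.** The protocol speaks of time periods, not sessions. A reader might infer that about 99% of sessions are certainly lost. That holds only for one session per period; with a month per period the figure is 83%, and the loss of power on the average rate is then about 14 percentage points (84% against 70%). This stands, and the range has to be given. It does not rescue the first half-year, which is uncounted on each of these readings.

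**Link to the complication hypothesis.** A reader might take peri-needle bleeding to be a stated component of the second hypothesis. The documents do not say so. It is a cannulation-related secondary outcome and plausibly belongs there, but that is inference.

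**Invisible harm.** A reader might also conclude that harm during the change-over would be missed altogether and reported as no difference. That goes too far. Hematoma or infiltration, inflammation, infection and bacteremia are outside the three-period restriction, each treatment is preceded by an examination, and bleeding that requires surgery is a referral criterion. What is lost is the count of peri-needle bleeding itself.

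**Deliberate choice.** The data collection spreadsheet has separate sheets for changes during follow-up and for semester data, which is consistent with planned collection in two tiers. This explains the schedule but does not justify placing an event in the tier meant for periodic measurements.

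**Burden.** One spreadsheet entry per session would mean up to 156 × 200 = 31,200 entries, and the document does not describe a VASACC field for bleeding. This is a fair objection to a tick at every session. It has much less force against logging incidents only: at the assumed risks that is about 312 + 624 = 936 entries.

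**Conclusion.** The point holds as a badly chosen recording rule for one secondary outcome. Followed exactly, the plan leaves 83% to 99% of follow-up sessions unobserved for peri-needle bleeding (one month to one session per period) and counts nothing until about month 6. Patients who leave before then add no post-baseline data. The share rests on three sessions a week for 52 weeks and on the assumed period length.

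The power figures are illustrative: the bleeding risks and the between-patient variance are assumptions with no source in the document. The direction is the same on every reading tried, but the size of the loss depends strongly on how long a period is. The primary outcome is not affected, and three time points remain a reasonable choice for the measured variables on the list. The change is worth making because it is cheap and specific.

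**What to change.** 1. In the Intervention section, remove peri-needle bleeding from the variables restricted to three time periods. A baseline record before the start can be kept.
2. State that each incident is logged, with its date, in the existing session record when it occurs, from the start of the study to the end of the patient's follow-up. Transfer these entries to the sheet for changes during follow-up.
3. In the Statistical analysis section, name peri-needle bleeding among the outcomes reported per 1000 days of AVF, alongside hematoma.
4. Add a descriptive summary by arm for the early period after the switch, with its length fixed in advance by the study team. The protocol gives no duration for the formation of the sites.
5. For any variable that stays on the three-period schedule, say how many sessions a time period covers.

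**Cost.** Modest extra recording and transcription to the Excel spreadsheet, possibly with a field to add in VASACC. By definition a nurse already attends to each incident, so no further staff or procedure is needed.
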